### Implementation {16c}

The randomization sequence will be generated centrally by the central study coordinator prior to trial initiation. Sealed envelopes will be prepared, shuffled independently by research nurses, and distributed to the participating sites. Participants will be enrolled locally by the treating surgeon or research nurse.

## Assignment of interventions: blinding

### Who will be blinded {17a}

The outcome assessors and participants will be blinded during the entire follow-up ending at 3 years after the surgical PEH repair. The operation report, with information on the specific type of repair performed, will not be included in the digital patient chart. Instead, a hard copy with information about the study group allocation will be kept in a sealed envelope, which is filed in a locked archive.

### Procedure for unblinding if needed {17b}

Unblinding is permissible if emergencies in the clinical management of the participant so require. Unblinding is performed by opening the sealed envelope, whereupon the procedural information is added to the medical records.

## Data collection and management

### Plans for assessment and collection of outcomes {18a}

Participants will undergo a study-specific low-dose CT scan of the upper abdomen and lower thoracic cavity at 1 and 3 years, with a permissible variation of ± 3 months from the specified time points. The CT protocol can be found in Supplement A. If a participant undergoes a clinically indicated CT scan that includes the upper abdomen and lower thoracic cavity within the specified time frame, the study-specific CT scan may be omitted. The CT scans will be reviewed by a specialized radiologist, blinded to the participants’ group allocation, to assess for recurrence.

Postoperative data including length of stay, complications, and reoperations will be collected by a research nurse or research fellow 30 days postoperatively. Severity of complications is graded according to the Clavien Dindo classification [34].

Patient-reported outcome measures (PROMs), including quality of life and the severity and frequency of symptoms, will be assessed at baseline, 3 months, 1 year, and 3 years. Health-related quality of life will be assessed with the Swedish version of the Short Form-36 (SF-36) questionnaire (RAND Corporation). SF-36 consists of 36 items grouped in eight domains, which can be summarized to mental and physical component scores [39–42].

The Gastrointestinal symptom rating scale (GSRS) measures symptoms of reflux, abdominal pain, indigestion, diarrhea, and constipation. The questionnaire consists of 15 items and uses a 7-point Likert scale, with 1 representing no symptoms and 7 representing severe symptoms. Scores are summarized for each of the five domains [38, 39].

The Dakkak dysphagia score assesses dysphagia. Participants report frequency (never, sometimes, or always) of dysphagia when eating nine types of solid, mashed, and liquid food. The generated score ranges from 0 to 45, where we will reverse the original scoring as done in previous studies, so that a higher score indicates more severe dysphagia [36, 37].

Additionally, a specific questionnaire will be used to assess the frequency of specific symptoms of heartburn, reflux, chest pain, dysphagia, globus sensation, respiratory symptoms, nightly cough, odynophagia as well as difficulty vomiting or belching.

The questionnaires will be made available to participants as hard copy or digital, depending on their preference. Participants will receive reminder letters by regular mail to encourage timely completion and submission of the forms.

### Plans to promote participant retention and complete follow-up {18b}

The questionnaires for postoperative follow-up are sent to the participants either by mail or electronically as preferred. If the forms are not completed and returned properly, a reminding letter will be sent by regular mail. If this is unsuccessful, a research nurse, research fellow, or surgeon will contact the participant by phone. The computed tomography at 1 and 3 years will, whenever possible, be performed at the participant’s local hospital to improve convenience for the participant.

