### Concealment mechanism {16b}

Allocation will be concealed using sealed, opaque, sequentially numbered envelopes. The envelopes will be opened in the operating theatre after induction of anesthesia, immediately prior to commencement of the procedure.

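### The retention plan lets a surgeon, not excluding the one who operated, phone participants about incomplete symptom and quality-of-life forms, which leaves the blinding of these secondary outcomes unguarded

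*Protocol article*

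**What the plan says.** All references are to the protocol article.

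- **Blinding, {17a}:** "The outcome assessors and participants will be blinded during the entire follow-up ending at 3 years after the surgical PEH repair". Surgeons are not on this list. The same section adds a safeguard: "The operation report, with information on the specific type of repair performed, will not be included in the digital patient chart". The allocation record is held on paper, sealed and locked away.
- **Concealment, {16b}:** "The envelopes will be opened in the operating theatre after induction of anesthesia, immediately prior to commencement of the procedure". The operating surgeon then carries out the allocated repair and so knows the arm.
- **Retention, {18b}:** "The questionnaires for postoperative follow-up are sent to the participants either by mail or electronically as preferred". The next step is a letter: "If the forms are not completed and returned properly, a reminding letter will be sent by regular mail". If that fails, "a research nurse, research fellow, or surgeon will contact the participant by phone".
- **Outcome collection, {18a}:** the forms are SF-36, GSRS, the Dakkak dysphagia score and a symptom-frequency questionnaire, at 3 months, 1 year and 3 years after surgery. For the primary outcome, "The CT scans will be reviewed by a specialized radiologist, blinded to the participants’ group allocation, to assess for recurrence". Complications and length of stay at 30 days are collected by a research nurse or research fellow; no surgeon is named.

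**The concern.** The list of permitted callers in {18b} is wider than the blinding in {17a} can safely bear. One of the three roles includes the person who performed the allocated operation and remembers it. The call is made because a form is missing or incomplete, so its subject is the participant's own report of symptoms and quality of life. A caller who knows the arm could let it slip, or could colour how the participant answers.

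These are secondary outcomes, but they matter to the interpretation. The Discussion notes that many recurrences cause few or no symptoms, and it relies on the patient-reported measures to show whether a difference on CT is clinically relevant. A self-reported measure has no later blinded reading that could correct an influence on the answer. Any such influence would fall only on participants who needed a call.

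This is not a detail that a condensed article has merely left out. The article states who may call, and the stated rule is too broad.

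**Working it through.** **1. Does any figure in the plan bear on this?** No. The stated sample size reproduces: 62 per arm for 30% versus 10%, two-sided α 0.05, with power 80.3% at that size. Inflating for 15% loss gives 124 / (1 − 0.15) = 146, against a target of 150. Changing who makes the calls alters none of this.

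**2. The sections side by side.**

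| Question | What the article says | Consequence |
|---|---|---|
| Who knows the arm? | Envelope opened in theatre ({16b}) | The operating surgeon does |
| Who must not know? | Participants and outcome assessors, to 3 years ({17a}) | Surgeons are outside the promise |
| Who may call? | Nurse, fellow or surgeon ({18b}) | No condition on knowledge of the arm; the operating surgeon is not excluded |
| What triggers the call? | Forms still outstanding after a letter ({18b}) | The call concerns self-reported outcomes |
| May answers be taken by phone? | Not stated; forms are paper or digital ({18a}) | Neither provided for nor ruled out |
| Would a surgeon who did not operate know? | Operation report kept out of the digital chart ({17a}) | Not normally |

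The open route is therefore narrow: the caller is the operating surgeon (or someone else who knows the arm), and the call goes beyond a neutral prompt.

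**3. Why the size cannot be computed.** If only one arm's answers shift, the bias in a mean difference is

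bias = (share of forms needing a call) × (share of those calls made by someone who knows the arm) × (shift in those answers, in SD).

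The article gives none of the three factors. Purely as assumptions, take a call share of 15–30% and a shift of 0.3–0.5 SD:

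- Participants called, of 150 / 2 = 75 per arm: 0.15 × 75 ≈ 11 to 0.30 × 75 ≈ 23 per time point.
- Every call made by someone who knows the arm: 0.15 × 1 × 0.3 = 0.045 SD to 0.30 × 1 × 0.5 = 0.15 SD.
- One third of calls so made: 0.045 / 3 = 0.015 SD to 0.15 / 3 = 0.05 SD.
- Reminder-only calls with no effect on the answers: 0 SD.

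The range runs from zero to 0.15 SD and depends wholly on what was assumed. It shows that the effect would be modest even in the unfavourable scenario. It is not an estimate for this trial.

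**The case against.** A reader might infer that {18b} contradicts {17a}, so that the protocol itself breaks its blinding. The documents do not support that. Surgeons are not among those to be blinded. The participant rates these scales and stays blinded unless told the arm. Both sections can be followed to the letter.

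Other points on that side also stand:

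- The text says only surgeon. A colleague who did not operate would normally be unaware of the arm, because the operation report is kept out of the chart.
- The call sits in a section on retention, as the last step after a letter. Nothing describes completing a questionnaire by phone, so that part of the mechanism is conjecture.
- The call has a clear benefit: fewer missing questionnaires. It would be wrong to say that nothing is gained by calling.
- Call scripts and delegation of tasks commonly sit in a full protocol or manual, and their absence from an article is no fault.

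These points reduce the concern to a risk but do not remove it. The safeguard in {17a} protects against reading the chart, not against the operating surgeon's memory. The benefit comes from the call, not from having a surgeon who knows the arm make it, since nurses and fellows are already listed. The article also applies a tighter rule elsewhere, with a nurse or fellow collecting the 30-day data and an explicitly blinded radiologist reading the scans.

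**Conclusion.** The point holds as a low-cost improvement. Section {18b} permits a caller who knows the allocation, and so leaves the blinding stated in {17a} unguarded for the self-reported secondary outcomes. It is a risk and not a shown breach. For it to cause harm, the operating surgeon or another person who knows the arm must make the call, and the call must affect what the participant knows or answers. The documents do not say that either happens, and they do not exclude either.

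The size cannot be computed from the documents. The primary CT outcome, the sample size and the primary analysis are unaffected.

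**What to change.** Amend the sentence in {18b} so that calls about questionnaires are made only by a research nurse, research fellow or other staff member who does not know the participant's allocation, and never by the operating surgeon. If any answers are taken by phone, record the mode of completion for that form, so that those responses can be identified later.

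The cost is one sentence and slightly less flexibility in who makes the call. The nurses and fellows are already among the permitted callers. The design, sample size and analysis do not change. Recruitment is expected to run to the end of 2026, so 3-year forms for the last participants fall due around the end of 2029 (2026 + 3), and a change made during the trial would still cover the follow-up to come.

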### Data management {19}

Two methods of data entry will be used to maximize convenience for participants and research staff. Data will either be entered directly in an electronic case report form or on paper forms. Pseudonymized paper forms will be securely stored at each center until they have been fully completed, after which they will be sent to the research coordinator for manual entry into the database. All manually entered data will be double-checked for accuracy. Data will be stored in a pseudonymized database on protected servers with restricted access at Ersta hospital.

### Confidentiality {27}

Screening logs and identity logs will be kept in locked storage at each participating site. Pseudonymized data will be stored in a database at Ersta hospital.

### Plans for collection, laboratory evaluation, and storage of biological specimens for genetic or molecular analysis in this trial/future use {33}

No biological specimens will be collected.

## Statistical methods

### Statistical methods for primary and secondary outcomes {20a}

Analyses will be performed on an intention-to-treat basis. Descriptive statistics will be used to present overall and group-wise data.

The primary outcome will be analyzed using logistic regression with treatment group as the main independent variable, with pre-specified co-variates including age, BMI, and hiatal area.

Secondary categorical outcomes will be analyzed using logistic regression and continuous outcomes using linear regression. Continuous outcomes with repeated measurement will be analyzed using linear mixed-effect models.

Exploratory post hoc analyses will assess the association between surgeon experience, defined as the number of prior paraesophageal hernia repairs performed, and primary and secondary outcomes.

All analyses will be performed using R Statistical Software (version 4.4.1, 2024–06–14, R Core Team, Vienna, Austria).

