### Sample size {14}

Previous studies have suggested recurrence rates after paraesophageal hernia repair ranging from 7 to 66% [15–20]. We have estimated the recurrence rate to be 30% in the control group and hypothesize that this can be reduced to 10% with the addition of gastropexy. With an α of 0.05 and a power of 80% (β = 0.2), we calculate a required sample size of 62 participants per arm, yielding a total of 124 evaluable participants. To account for an estimated 15% loss to follow-up, based upon previous studies with similar follow-up at the same institution, we aim to include 150 participants. The primary analysis will use multiple imputation under a missing-at-random assumption to include all randomized participants; this approach is expected to preserve the planned power under the anticipated missingness.$$\begin{aligned}n&=\left[\sqrt{\frac{\left(0.3+0.1\right)}{2}\left(1-\frac{\left(0.3+0.1\right)}{2}\right)\left(1+\frac{1}{1}\right)}\ 1.96\ \right.\\&\left.+\ \sqrt{0.3\left(1-0.3\right)+\frac{0.1\left(1-0.1\right)}{1}}0.84\right]^{2}/{0.2}^{2}\approx 62\end{aligned}$$

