### Recruitment {15}

This multicenter trial currently includes six centers, with additional centers being invited to participate. The annual volume of PEH repairs varies across the centers, but the majority perform more than 20 cases annually. Based on these volumes, we anticipate reaching our target of 150 participants included within the projected recruitment period of 2–3 years.

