## Assignment of interventions: allocation

### Sequence generation {16a}

Participants will be assigned to either the control or intervention group with a 1:1 allocation ratio. A computer-generated randomization list in blocks of 10 for high-volume centers and six for low-volume centers will be used. Stratification will be performed by center only.

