### Methods in analysis to handle protocol non-adherence and any statistical methods to handle missing data {20c}

With the randomization and intervention taking place in the operating room, we expect no protocol non-adherence. Prior to surgery, we will ensure that all preoperative questionnaires are completed, which should reduce the risk of missing baseline data. We will handle missing primary outcome data using multiple imputation by chained equations (MICE) under a missing-at-random assumption. The imputation model will include treatment group and pre-specified prognostic variables (including baseline characteristics and any available intermediate/follow-up measurements) to generate m imputed datasets; each dataset will be analyzed using the planned regression model for the dichotomous outcome (e.g., logistic regression), and estimates will be combined using Rubin’s rules.

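### Centre is the only stratification factor but is named in neither the primary model nor the imputation model; if recurrence differs between centres, the test is conservative and a little power is forgone

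*Protocol article*

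**What the plan says.** Under Sequence generation {16a} the protocol article states: "Stratification will be performed by center only". The same section gives the blocking: "A computer-generated randomization list in blocks of 10 for high-volume centers and six for low-volume centers will be used". Under Recruitment {15}: "This multicenter trial currently includes six centers, with additional centers being invited to participate".

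Under Statistical methods for primary and secondary outcomes {20a}, the primary outcome is analysed by "logistic regression with treatment group as the main independent variable, with pre-specified co-variates including age, BMI, and hiatal area". Section {20c} says of missing primary outcome data: "The imputation model will include treatment group and pre-specified prognostic variables (including baseline characteristics and any available intermediate/follow-up measurements").

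Centre, the one factor used to structure the allocation, is named in neither description. Both lists are introduced by the word *including*, so neither expressly rules it out.

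Sample size {14} rests on a comparison of two proportions without adjustment: "With an α of 0.05 and a power of 80% (β = 0.2), we calculate a required sample size of 62 participants per arm".

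**The concern.** Blocking within centre balances the arms within each centre. If recurrence differs between centres, that balance removes the between-centre part of the variability of the treatment comparison. A model without centre still counts that part as noise, so its test statistic varies less than its nominal distribution says. The test then rejects too seldom under the null and gives away some power under the alternative.

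The document offers some reason to expect centre differences, although it does not quantify them. Centre volumes vary, more centres may join, an experienced surgeon may operate or only supervise, an extra anterior crural closure is discretionary, and the trial itself plans to relate surgeon experience to outcome.

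The imputation raises a related question. If missing one-year CT scans cluster by centre and recurrence also differs by centre, the missing-at-random assumption is easier to defend with centre in the imputation model.

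**Working it through.** **1. The plan's own figure.** With 30% v 10%, mean rate 0.2, and the constants 1.96 and 0.84 from Sample size {14}:

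n = [1.96·√(2·0.2·0.8) + 0.84·√(0.3·0.7 + 0.1·0.9)]² / 0.2² = [1.1087 + 0.4601]² / 0.04 = 61.5, so 62 per arm and 124 in all.

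Power at 62 per arm is 80.3%. Allowing for 15% loss gives 124/0.85 = 146. The stated 150 leaves 127.5 evaluable. The figures reproduce, and they assume no gain from adjusting for centre.

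**2. Expected events.** 62·0.30 + 62·0.10 = 24.8.

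**3. Simulation.** Inputs from the document: 124 evaluable, six centres, blocks of 10 or 6, 1:1 allocation, 30% v 10% (or 20% in both arms for the null), two-sided 5%. Assumptions not in the document:
- centre sizes 34/26/20/16/16/12;
- between-centre standard deviation (SD) of recurrence on the logit scale, 0 to 1.5. SD 0.5 corresponds to control recurrence of about 20% to 40% across ±1 SD; SD 1.0 to about 12% to 50%.

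There were 4,000 to 6,000 runs per scenario. Monte Carlo error is about 0.3 points for type I error (√(0.05·0.95/4000)) and 0.5 points for power (√(0.8·0.2/6000)). Age, BMI, hiatal area and imputation were not simulated.

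Logistic regression without centre v with centre as fixed effects:

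| Between-centre SD | Type I error, fixed spread | Power, fixed spread | Power, randomly drawn centre effects |
|---|---|---|---|
| 0 | 4.7% v 5.0% | 80.9% v 82.0% | 79.8% v 81.0% |
| 0.5 | 4.2% v 4.9% | 80.7% v 82.6% | 81.1% v 82.8% |
| 1.0 | 3.2% v 5.0% | 82.3% v 86.0% | 79.1% v 82.5% |
| 1.5 | not run | 84.2% v 90.0% | 78.2% v 83.6% |

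With randomly drawn centre effects, type I error was 4.0% v 4.6% at SD 0.5 and 3.3% v 5.0% at SD 1.0. A separate simulation with randomly drawn effects, comparing no centre with centre stratification, gave 4.4% v 5.1% and 3.3% v 4.8%, with power 81% v 82% and 80% v 85%. A centre-stratified Mantel-Haenszel test (fixed spread) had type I error of 4.7% and 4.8%, and power of 82.6% and 86.0%, at SD 0.5 and 1.0.

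**4. Mechanism.** At SD 1.0 under the null, the Wald z without centre has standard deviation 0.928 instead of 1. A normal variable with that spread exceeds 1.96 in absolute value with probability 2·[1 − Φ(1.96/0.928)] = 2·[1 − Φ(2.11)] ≈ 3.5%, in line with the simulated 3.2%.

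**5. How much is due to centre.** Even at SD 0 the two models differ by about 1 point of power (82.0 − 80.9 = 1.1), from small-sample conservatism of the Wald test. The gap is 1.7 to 1.9 points at SD 0.5 and 3.4 to 3.7 at SD 1.0 in the table. Net of that first point, little at SD 0.5 is due to centre.

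**6. Sparsity of full centre adjustment.** Treatment plus three covariates gives 24.8/4 = 6.2 events per parameter. Five centre indicators make it 24.8/9 = 2.8. With the assumed sizes and 30% v 10%, at least one centre has no events in 24% of runs at SD 0.5 and 55% at SD 1.0.

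**The case against.** **The lists are open and the article is condensed.** Centre could be among the unlisted covariates, or count as a baseline characteristic in the imputation, and a full protocol or analysis plan may say so. This stands against any claim that centre is excluded. It does not remove the point: the article chose to name its pre-specified covariates, listed three that play no part in the randomisation, and left out the one that does. A reader who fits the model as described omits centre.

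**A reader might infer that the reported standard errors and intervals are too wide.** In a logistic model that is not so in the ordinary sense. At SD 1.0 the median reported standard error of the log odds ratio is smaller without centre (about 0.51 v 0.57). Adding centre raises it and moves the log odds ratio from −1.39 to −1.65. The standard error without centre is too large only relative to the sampling variability under stratified randomisation.

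**A reader might infer that the trial is underpowered.** It is not. Power without centre stays at about 78% to 84%; what is forgone is a gain the sample size never counted on.

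**Centre differences may be small.** Operations are performed or supervised by surgeons with more than 25 repairs, technique is harmonised with video review, and CT scans are read blinded. Hiatal area may absorb some case-mix. All of this is fair; the simulation omits the covariates and so may overstate the loss. Scans are done at the participant's local hospital where possible, so missing scans need not follow the operating centre. The imputation point is reasoning only, with no calculation behind it.

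**Conclusion.** The point holds as a matter of calibration, efficiency and pre-specification. The sole stratification factor is unnamed in both models. If the primary model uses the named covariates only and recurrence differs between centres, the treatment test is conservative: type I error is about 3.2% to 4.4% and about 2 to 4 points of power are forgone, under assumed between-centre logit SDs of 0.5 to 1.0. With no centre differences nothing material is lost.

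These sizes rest on an assumed between-centre spread, assumed centre sizes, complete data and no baseline covariates. The direction does not depend on the exact centre sizes. The validity of a positive result is not threatened. The change is worth making because it is cheap and centre is known for every participant.

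**What to change.** State in the primary analysis that the treatment comparison accounts for centre, through a centre random intercept or centre-stratified estimation (conditional logistic regression, or Mantel-Haenszel), rather than a full set of centre indicators. Conditional logistic regression keeps age, BMI and hiatal area in the model; a plain Mantel-Haenszel analysis does not. The random intercept was not simulated here, so its behaviour with six centres and about 25 events should be checked before it is chosen.

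Pre-specify how very small or late-joining centres are pooled, without reference to outcome by arm. Name centre among the variables of the chained-equations imputation, using the same pooling.

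Cost: a few sentences, a little more analysis work and no new data. The odds ratio becomes conditional on centre, so it will lie further from 1 where centres differ, with a somewhat larger reported standard error on the log-odds scale. Recruitment is expected to run to the end of 2026 and no interim analysis is planned, so this can be settled before the primary outcome is analysed.
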